## Abstract

**Background:**

The prevalence of depressive symptoms among youth seems to be increasing. Depression among youth is associated with poorer academic performance and social relationships. Preventive interventions for youth with elevated depressive symptoms are essential. The STARr training was found to reduce depressive symptoms in youth; however, it was too linguistic and could be enhanced in terms of gender and cultural background. This study will examine whether a simplified, adapted modular CBT training (STARr 2.0) is effective in reducing depressive symptoms and co-occurring anxiety symptoms among youth with depressive symptoms. Further, this study will assess whether the module sequence preferences of adolescents, trainers, or data predict the outcome depressive symptoms. Additionally, alliance, motivation, and expectation of the treatment will be assessed as predictors. Last, we will examine moderators (age, gender) and change mechanisms (problem solving, cognitive restructuring, behavioral activation, and stress).

**Methods:**

An n-of-1 study with a single-case observational design with a baseline and effect phase will be employed. The baseline phase starts three weeks before the training. We aim to include 30 adolescents between 12 and 20 years at two mental health organizations. All participants receive the adapted STARr-training in groups of six to eight participants. The training consists of 12 hourly sessions provided by a trained trainer. Participants receive in total three short questionnaires per week and six longer questionnaires (start baseline, before the start of the training, and after each module). The primary outcome is depressive symptoms and secondary outcomes are anxiety, stress, satisfaction with the training, and individual and societal functioning.

**Discussion:**

The findings of this study will provide insight into whether an adapted simplified version of the STARr training is effective in reducing depressive symptoms and will also provide insight into change mechanisms and potential subgroup differences. If the adapted version is effective in reducing depressive symptoms, then the training can be used widely by mental health professionals.

**Trail registration:**

Overview of Medical Research in the Netherlands (*OMON).* Registration number NL-OMON58273, registration date: 4 December 2025.

## Background

### Depression and cognitive behavioral therapy

Depression is highly prevalent among youth [1, 2]. Meta-analytic studies show that within Europe, 1,7% of children and adolescents suffer from a depressive disorder [2], and around 14% of youth worldwide suffer from subclinical depression [3]. Also, in the Netherlands, the prevalence of mental health problems seems to have increased between 2017 and 2022 [4, 5]. Depression in youth often co-occurs with anxiety and stress symptoms [6, 7], and is associated with severe negative consequences such as poorer academic performance [8, 9], poorer social relationships [10], and suicidal ideation [11]. Moreover, youth depression is associated with unemployment, depression, anxiety, and suicidality in adulthood [12, 13]. Societal impact of depression is also high, as societal costs amount to 38 million euro annually for clinically depressed youth [14] and 42 million euro annually for subclinical depressed youth [15]. Given the increase in prevalence in mental health problems and the detrimental consequences of untreated depression, preventive interventions for youth with elevated depressive symptoms are essential.

Cognitive behavioral therapy (CBT) is the first choice of psychotherapy and has proven to be effective in reducing subclinical levels of depressive symptoms in adolescents [16–18]. However, not all adolescents with depressive symptoms seem to benefit from receiving CBT [17, 19]. Therefore, it is essential to assess the requirements for adapting CBT for adolescents. In response to the need to improve therapy outcomes, clinicians and researchers have moved away from the one-size-fits-all approach for CBT and have developed personalized interventions for youth [20]. A meta-analysis showed that personalized interventions seem to improve psychological therapy outcomes compared to standardized therapy [21]. Over the last few decades, evidence has been found for methods of both tailoring treatment to the individual based on personal characteristics, as well as adapting the treatment during the therapy process [20]. These personalized interventions include modular therapy, shared decision making, individualized metrics, and adaptations regarding inclusivity and diversity [20, 22].

One method to optimize and personalize treatments for youth is a modular approach. In a modular approach, the sequence of CBT modules can be adjusted, omitted, or repeated based on the client’s needs, preferences, and characteristics [20, 23]. Several studies found that modular psychotherapy (e.g., CBT) was associated with a decrease in depressive or anxiety symptoms in young people [24–26]. Moreover, modular psychotherapy was associated with better treatment outcomes than non-modular psychotherapy among youth with depressive or anxiety symptoms [27].

Our previous study examined a modular preventative intervention, based on CBT, for youth aged between 10 and 20 years old with elevated depressive symptoms. This intervention is called STARr (Solve (problem solving), Think (cognitive restructuring), Act (behavioral activation), Relax (relaxation), and repeat) [28]. For further details of this study, see van den Heuvel et al. [26, 28, 29]. A randomized controlled microtrial was conducted, including 282 participants between the ages of 11 and 18 years old (*M* = 13.82, *SD* = 1.48) with elevated levels of depression. It was found that STARr significantly reduced depressive symptoms when adolescents received all four modules [26]. The distinct modules did not significantly reduce depressive symptoms (after three sessions), and the reduction of depressive symptoms was not affected by the sequence of the modules [26]. The reduction of depressive symptoms was also not moderated by gender, age group, or severity of depressive symptoms [29]. This suggests that modular CBT is promising in reducing depressive symptoms in a wide range of youth.

A second way to further optimize and personalize CBT is the use of shared decision-making in therapy [30]. Shared decision-making is a process in which the clinician and client discuss treatment decisions and plans and reach consensus [31]. Shared decision-making can be used for deciding the sequence of modules in a modular approach, such as the STARr training. Systematic reviews on shared decision making and patient preference found little evidence that shared decision-making improves mental health outcomes (e.g., depression, quality of life, anxiety) [30, 32–34], but found an increase in treatment adherence and satisfaction [30, 33, 35]. Most of these studies have included adult samples. Further studies are needed to examine whether shared decision-making improves mental health outcomes in youth, preferably including an assessment of fidelity and a clear description of decision-making methods [30, 32].

Shared decision-making is based on the clients’ and therapists’ perspectives; however, decision-making can also be informed by data. Statistical (data-driven) models or algorithms (the Personalized Advantage Index: PAI) can guide the decision-making regarding the sequence of treatment elements or what treatment would likely be best for the client [22, 36]. Based on several characteristics of a client, the PAI can predict what sequences of modules would most likely lead to the most optimal treatment outcome for an individual [22]. This method could inform therapists in deciding on which module to use. Previous studies among adults have examined differences in outcomes predicted by the PAI and found that participants who were assigned to the predicted optimal treatment had better treatment outcomes (e.g., lower predicted depression scores) than those who were not [22, 37–39]. Nevertheless, a systematic review on decision-making in modular treatment for youth showed that none of the treatments utilized statistical models or algorithms to make decisions in treatment [40]. This indicates that evidence of data-driven decision making is missing for youth, and it is necessary to assess whether algorithms can aid in predicting the optimal module sequence in modular treatments for youth. Furthermore, we want to explore whether other treatment characteristics (besides preference) predict the reduction in depressive symptoms; these predictors are motivation, expectancy, and alliance.

A third method to optimize and personalize interventions is by making them more inclusive. Evidence suggests that when CBT is inclusive of diverse educational levels, cultural backgrounds, and gender, alliance and satisfaction are rated higher by participants [41–44].

Both alliance and satisfaction are associated with better clinical treatment outcomes [45, 46].

Evaluation of the STARr intervention revealed that not all youth seemed to benefit at an individual level [26]. Focusgroups with youth and trainers showed, among others, that the training and booklets were too linguistic, and that the sessions could be more active (de Lange et al., in preparation). Additionally, the interventions’ inclusivity could be improved regarding cultural background and sexual and gender identity. Thus, to further optimize and personalize the STARr intervention, the intervention was adapted and simplified (de Lange et al., in preparation).

Last, examining for whom and how CBT works could also aid in improving treatment [47, 48]. A systematic review on moderators of treatment outcomes of psychological interventions found only one study that indicated that CBT had better treatment outcomes for girls compared to care as usual, but other studies did not find moderation effects for gender [49]. This is in line with van den Heuvel and colleagues’ study [29], which did not find differences for gender when comparing behavioral and cognitive modules. Regarding adolescents’ age, no moderation effect was found in studies in the systematic review [49], and no differences for age were found when comparing behavioral and cognitive modules in van den Heuvel and colleagues’ study [29]. In the current study, we will examine whether certain module sequences lead to better treatment outcomes depending on gender and age.

With respect to mechanisms of change in psychotherapy, a meta-analysis on CBT for depression in adults found small-to-medium effect sizes for cognitive processes (e.g., changes in negative cognitions) and small effect sizes for behavioral strategies (e.g., changes in activation) were observed [50]. Huibers and colleagues [48] suggest that besides cognitive and behavioral mechanisms of change, other processes might act as a mechanism of change, such as therapeutic alliance. Thus, it is important to assess mechanisms of change (e.g., cognitive restructuring and behavioral activation) for the STARr training.

In short, optimizing and personalizing CBT interventions is necessary to promote adherence and motivation. Several possibilities exist to optimize and personalize cognitive behavioral therapy for youth with depressive symptoms. For example, utilizing a modular approach, utilizing shared decision making in therapy, making interventions more inclusive, and lastly gaining insight in what works for whom.

### Current study and objectives

The current study is a follow-up study of the “STARr-project: Preventing depression in youth” [28], which was conducted between 2017 and 2020.

The current study will investigate:

whether a simplified, adapted and more personalized version of the modular STARr-training (STARr2.0) is effective in reducing depressive symptoms (and comorbid stress and anxiety symptoms) among adolescents aged between 12 and 20 years. The effect size of the reduction in depressive symptoms will be compared with the effect size from the previous STARr study. Additionally, treatment satisfaction and drop-out will be assessed as secondary outcomes. Additionally, the descriptive statistics of satisfaction and drop-out will be compared to the previous STARr study.whether the preference of the adolescents, the preference of the trainer, or a data-driven model regarding the sequence of modules best predicts a reduction in depressive symptoms (and comorbid stress and anxiety symptoms). And whether treatment characteristics (motivation, expectancy, and alliance) predict a reduction in depressive symptoms.for whom and under which circumstances (moderators; gender and age) the modules of the STARr training works best andwhich mechanisms of change drive the reduction in depressive symptoms (mediators; problem solving, negative thinking errors, behavioral activation, and stress).

To assess the adapted modular approach (STARr2.0), a single case observational design (SCOD) will be utilized [51]. A single case design is highly feasible for clinical studies, because it allows for evaluating the efficacy of individual trajectories, and thus small samples [52, 53]. We will use an AB-design with a non-randomized introduction of the intervention.

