### Sample size and power calculation

We used a power calculation application for single-case designs [59] to calculate the expected power when utilizing a permutation distancing test with a total of 30 participants who complete the study. Participants will receive a total of 45 repeated measurements, of which 18 belong to Phase A and 27 to Phase B. With a mean difference of 1.5 units (small treatment effect) between phases A and B (SD phase A = 3 and SD phase B = 3), and a missing percentage of 20% and autocorrelation level of 0.2, the power would be 79%. It is important to note that this is the calculated overall power is calculated for the group. The power per individual could be lower or higher, depending on, e.g. the percentage of missing observations and the level of autocorrelation between observations.

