### Statistical analyses

#### Primary and secondary outcomes

The Permutation Distancing Test (PDT) [51] will be utilized to assess mean level differences of the primary outcome (*depressive symptoms)* between the baseline phase and the effect phase per participant. For this purpose, we will use the repeated measurements data (i.e., the 3 ESM measurements per week). The PDT was developed to evaluate individual treatment effects in SCODs. It is a nonparametric permutation test that accounts for autocorrelation by applying stepwise down-sampling while using all available observations to create sufficient ‘distance’ between observations (for more information, please see Vroegindeweij et al. [51]. In the PDT, the moment (the lag) is defined at which a treatment effect is expected to start. This marks the beginning of Phase B (i.e., the effect phase). The observations before Phase B are part of Phase A (i.e., the baseline phase) [51]. We expect that Phase B will start after the first module (three weeks after the start of the training). Hence, we will use a lag of 3 in our analyses for all participants. The PDT analyses will be performed with *R*-package *“pdt”* in Rstudio. The *R*-package includes a function to plot the individual time series to inspect the data for (linear) trends first. We shall use this function before performing the PDT analyses.

In addition, mean level differences of the secondary outcomes (*stress*,* anxiety*, and *individual and societal functioning)* will be assessed. Further, the descriptive statistics of the secondary outcomes, *satisfaction with the training and drop-out*, will be provided and compared with *satisfaction with the training* results from the previous STARr study [26].

Last, the youth’s, trainers’, and data-driven preferences of module sequences, and treatment characteristics (*motivation for treatment*,* therapeutic alliance*,* and participants’ expectancy of each module)* will be assessed as predictors for change in depressive symptoms. The mean level differences and predictions will also be performed in RStudio.

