#### Mediation and moderation analyses

Next to analyzing mean level differences, *problem-solving*, *negative cognitive errors*, *behavioral activation*, and *stress* are assessed as mediators in the relation between depressive symptoms at T1 and T5. Assessing these as mediators will inform what mechanisms contribute to changes in depressive symptoms [93]. In addition, *gender* and *age* will be assessed as moderators. We will assess whether the interaction between these moderators and module sequence leads to different outcomes. We are only able to assess the moderators when various module sequences are executed during the study. Mediation and moderation analyses will be conducted in RStudio using multilevel regression modeling techniques [93–95].

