This study also has several strengths. We will evaluate the adapted STARr intervention in existing mental health care settings among youth who searched for mental care themselves or together with their parents. Participants will not be motivated by the compensation to enroll in the training because they first register to enroll in the STARr training and then they will be informed about the study. This might reflect best the group of youth who would generally enroll in the training, which enhances the external validity. Moreover, we use an innovative design in which we use input of the youth, trainers, and data to predict the best fit of modules for each participant. In addition, by using a single case design, participants are their own control condition, which allows all participants in the study to receive the care they need. Additionally, this design allows us to assess the change mechanisms that underlie the change in depressive symptoms, providing insight into what works for whom and why.

This study will provide insight into whether the adapted STARr training is effective in reducing depressive symptoms and co-occurring anxiety and stress symptoms. Moreover, it will provide insight into moderators and mediators. When the adapted STARr training is effective in reducing depressive symptoms and co-occurring stress and anxiety, the training can be provided widely to youth with elevated levels of depressive symptoms by trained mental health professionals in the Netherlands.

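### Objective 2 asks which of three sequence choices predicts best, but the article describes no comparison between them, varies the outcome between sections, and claims power for analyses that were never powered

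*Protocol article*

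**What the plan says.** Under Current study and objectives, four aims stand side by side. The second asks which of three sources of sequence choice (adolescent, trainer, data-driven model) "best predicts a reduction in depressive symptoms (and comorbid stress and anxiety symptoms"), and whether motivation, expectancy and alliance predict a reduction in depressive symptoms. The third concerns gender and age as moderators. The fourth asks which of four mechanisms drive the reduction.

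The later sections do not quite match this:

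- **Procedure** says that the three preferences serve as predictors of the study outcomes, in the plural and without naming them.
- **Primary and secondary outcomes**, under Statistical analyses, says that the preferences and treatment characteristics "will be assessed as predictors for change in depressive symptoms". It names depression only and describes no comparison between predictors.
- **Mediation and moderation analyses** says "We will assess whether the interaction between these moderators and module sequence leads to different outcomes". It adds that this is possible only if more than one sequence is actually delivered.
- **Sample size and power calculation** concerns the permutation distancing test "with a total of 30 participants who complete the study" and concludes that "the power would be 79" per cent.
- **Discussion** names 80% completed questionnaires from 30 participants as the condition for adequate power in every planned analysis. It later describes the design as "providing insight into what works for whom and why".

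Exploratory wording appears once, in the Background, and covers motivation, expectancy and alliance only.

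**The concern.** The question in objective 2 is comparative, while the described analysis is not. Three separate predictor assessments give three coefficients or p-values, and one of them is always the largest. Without an estimate of the differences and a rule for when no predictor stands out, the study will seem to have answered a question that its data may not be able to answer.

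Two further statements add to this. The outcome changes from section to section, so the preference that comes first for anxiety could be reported even if it does not come first for depression. The Discussion's power statement also invites readers to treat the predictor, moderator and mediator results as confirmatory, although none of them was powered.

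At stake is the conclusion on personalisation: whether future groups should follow the adolescent, the trainer or the algorithm. The Background reports that in the earlier trial of 282 participants the sequence did not affect symptom reduction and that gender and age group did not moderate it. A striking result from 30 participants would therefore call for caution.

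**Working it through.** **1. The plan's own power figure.** The inputs are 30 completers, "With a mean difference of 1.5 units (small treatment effect") and "SD phase A = 3 and SD phase B = 3", with 18 measurements in phase A and 27 in phase B, 20% missing and autocorrelation 0.2. The article states neither alpha nor the application's formula. Two-sided 5% is assumed here.

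- Paired test, d = 1.5/3 = 0.5, N = 30: Φ(0.5 × √30 − 1.96) = Φ(0.779) = 78.2% (75.4% with the t distribution).
- One person, normal approximation with 20% missing and variance inflation (1 + 0.2)/(1 − 0.2) = 1.5: about 22%.
- Thirty people pooled with the same effect in everyone: about 100%.

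Only the first comes near 79%, and it ignores the repeated measurements, the missing data and the autocorrelation, so it is not a true reproduction. This does not affect the point. On every version the figure concerns the phase comparison and no predictor, moderator or mediator.

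**2. What 30 participants can show about a predictor.** As an illustration, take a correlation r between a predictor and symptom change. Power = Φ(atanh(r) × √(n − 3) − 1.96).

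- r = 0.3: Φ(0.310 × 5.196 − 1.96) = 36%.
- r = 0.5: Φ(0.549 × 5.196 − 1.96) = 81%.
- Smallest r with 80% power: tanh((1.96 + 0.842)/5.196) = 0.49.

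**3. What they can show about a difference between predictors.** Suppose one choice shows r = 0.3 and another r = 0. The difference on the Fisher scale is 0.310.

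- If the two estimates are independent, SE = √(2/27) = 0.272 and the 95% interval is 0.310 ± 0.533, or −0.22 to 0.84.
- If the two estimates correlate 0.5, SE = √(2 × 0.5/27) = 0.192 and the interval is 0.310 ± 0.377, or −0.07 to 0.69.

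Both include zero, although a simple ranking would name the first choice as best.

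**4. Number of tests,** at one test per predictor and outcome:

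| Reading | Preferences | Treatment characteristics | Moderators | Mediators | Total |
|---|---|---|---|---|---|
| Objectives | 3 × 3 = 9 | 3 | 2 | 4 | 18 |
| Objectives, one sequence delivered | 9 | 3 | 0 | 4 | 16 |
| Analysis section | 3 × 1 = 3 | 3 | 2 | 4 | 12 |
| Analysis section, one sequence delivered | 3 | 3 | 0 | 4 | 10 |

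The Procedure wording could raise the total further, for example to 3 × 5 + 9 = 24 with five outcomes.

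**5. Chance of at least one false positive,** with every null true and 5% per test. For independent tests it is 1 − 0.95^k. For correlated tests it comes from simulating equicorrelated normal statistics.

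| Tests | Independent | Correlation 0.5 | Correlation 0.8 |
|---|---|---|---|
| 18 | 60% | 40% | 22% |
| 12 | 46% | 32% | 19% |
| 10 | 40% | 29% | 17% |

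With alpha at 0.01 or 0.10, the figure for 18 independent tests would be 16.5% or 85%.

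**The case against.** The strongest reply has four parts.

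- **The article is only a summary.** How the three predictors are compared, and how multiplicity is handled, may be set out in an analysis plan that is not shown. This stands for multiplicity: its absence here is no fault, and the rates above describe the size of the problem, not a missing adjustment. It stands only in part for the comparison. The article itself poses a best-of-three question, describes separate assessments, and gives three versions of the outcome.
- **Some ranking exists.** Depression is the primary outcome, with anxiety and stress secondary, and the abstract puts effectiveness first. This stands, so it would be wrong to say that the plan has no hierarchy. The ranking is of outcomes, however, and gives objectives 2 to 4 no exploratory status.
- **The test count is uncertain.** A reader might infer from the objectives that at least 18 tests will be run and that a false finding is likely. The documents do not support that. The analysis section gives 12, the moderator tests may not be possible, and at correlation 0.5 none of the counts from 10 to 18 reaches even odds. Pooling predictors, moderators and mediators into one family is also a choice.
- **The closing wording is mild.** To speak of insight is not to claim proof, and the recommendation for wide use rests on effectiveness alone. This stands, and changing that phrase would be mainly a matter of tone.

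None of this rescues the Discussion's power statement, which goes beyond the only calculation given.

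**Conclusion.** The point holds in this form: objective 2 is comparative and the described analysis is not, its outcome differs between three sections, and the Discussion claims power that the sample-size section does not provide. With 30 participants, power for a correlation of 0.3 is about 36%, and a difference between r = 0.3 and r = 0 has an interval that includes zero in both cases shown. Over 10 to 18 tests the chance of at least one false positive is about 40% to 60% if independent and 29% to 40% at correlation 0.5.

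These figures assume two-sided 5% per test (the article states no alpha), all nulls true, one test per predictor and outcome, and correlations as a stand-in for the eventual models. The primary phase comparison is not affected. The matter should be corrected because the conclusions about personalisation would otherwise be stated more firmly than the data allow.

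**What to change.** 1. In Current study and objectives, Procedure, and Primary and secondary outcomes, name change in depressive symptoms as the single outcome of the preference comparison. Stress and anxiety can stay as clearly subordinate descriptions.
2. Replace the best-of-three question by the estimated pairwise differences in predictive performance between youth, trainer and data-driven choice, each with a 95% interval. State that no best predictor will be declared if these include zero.
3. In Current study and objectives, Primary and secondary outcomes, and Mediation and moderation analyses, label objectives 2 to 4 as exploratory and report them as estimates with intervals.
4. In the Discussion, limit the power statement to the phase A versus B permutation test.

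No new data are needed. The existing predictor models remain, with the pairwise differences added. The cost is weaker claims for objectives 2 to 4.
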